**Table 5d – Schedule of visits (Group 4 – D112 boost)**

|                        | Online survey to establish eligibility | V1                          | V2                | V3               | V3a* (n=10)   | V3b* (n=10)    | V4                | V5                  |
|------------------------|----------------------------------------|-----------------------------|-------------------|------------------|---------------|----------------|-------------------|---------------------|
| Study timeline         | Up to D0 - 90                          | D0                          | 84                | D112             | D2 Post Boost | D7 Post Boost  | D140              | D364                |
| Study windows          |                                        | Within 90 days of screening | Day 84-98 post V1 | D112-140 post V1 | D2-4 after V3 | D7-12 after V3 | Day 21-35 post V3 | Day 334-394 post V1 |
| Informed consent       |                                        | X                           |                   |                  |               |                |                   |                     |
| Medical history        | X                                      |                             |                   |                  |               |                |                   |                     |
| Urinary pregnancy test |                                        | X                           |                   | X                |               |                |                   |                     |

CONFIDENTIAL

|                                          |  |   |   |                                       |   |   |   |   |
|------------------------------------------|--|---|---|---------------------------------------|---|---|---|---|
| (if female > 11yrs)                      |  |   |   |                                       |   |   |   |   |
| Physical examination                     |  | X |   | X                                     |   |   |   |   |
| Physical assessment (as required)        |  | X | X |                                       |   |   | X | X |
| Vaccination                              |  | X |   | X                                     |   |   |   |   |
| Safety bloods Group 4 subset only (n=20) |  |   |   | X – if allocated to V3a or V3b (n=20) | X | X |   |   |
| COVID-19 immunogenicity bloods           |  | X | X | X                                     |   |   | X | X |
| Diary card review                        |  |   | X |                                       |   |   | X |   |
| AE/SAE check                             |  | X | X |                                       |   |   | X | X |

In line with section 8.9, further additional visits may be required at the end of the trial, subject to approval of the IMP vaccine for use in this age group.

\*a subset of participants will be allocated to have safety bloods taken at only one of timepoints V3a, V3b, V4a, V4b.

xparticipants in group 3 will be allocated to either V5 or V6. Total number of blood draws in this group will not exceed 6

#### 7.4.5. 'Positive Pathway' for SARS CoV-2 infection

The parents or guardians of participants who are under 16/participants who are 16 and over who test positive for SARS CoV-2 infection in the community during the follow-up period will be instructed to contact the study team, who will then log the case on the eCRF.

#### 7.4.6. Medical notes review

With the participant's (if aged 16 and over) or parent/guardian's consent (and the participant's assent, if aged 11 and over), the study team will request access to medical notes or submit a data collection form for completion by attending clinical staff on any medically attended COVID-19 episodes. Any data which are relevant to disease enhancement (AESI) will be collected. These are likely to include, but not limited to, information on ICU admissions, clinical parameters such as oxygen saturation, respiratory rates and vital signs, need for oxygen therapy, need for ventilatory support, imaging and blood tests results, amongst others.

#### 7.4.7. Randomisation, blinding and code-breaking

Participants will be randomised on a 4:1:4:1 basis to receive ChAdOx1 nCoV-19 5.0x10^10vp/ 5.0x10^10vp (boost at D28) or MenB/MenB (boost at D28) or ChAdOx1 nCoV-19 5.0x10^10vp/ 5.0x10^10vp (boost at D84) or MenB/MenB (boost at D84). A block randomisation with block size of 10 will be applied. The randomisation will be stratified by recruitment site and age group.

The trial staff administering the vaccine will not be blinded. Vaccines will be prepared out of sight of the participant and syringes will be covered with an opaque object/material for administration to ensure blinding.

If the clinical condition of a participant necessitates breaking the code, this will be undertaken according to a trial specific working instruction and group allocation sent to the attending physician, if unblinding is thought to be relevant and likely to change clinical management. If a participant becomes eligible for routine immunisation then they will need to be unblinded, and if they were in the control group they will be advised to receive a COVID-19 vaccine as per NHS guidelines. They will also be offered the opportunity to complete their course of MenB vaccination if they have not already received their second dose. If participants were in the ChAdOx1 arm, they will be offered the opportunity, in the trial, to complete their course of ChAdOx1 vaccination, if they have not already received their second dose. All unblinded participants will be allowed to stay on in the trial for follow up visits, both for safety and immunogenicity data.

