## 10. STATISTICS

### 10.1. Sample size

The total sample size of this trial will be 261 with 60 participants in ChAdOx1 nCoV-19 groups and 15 in each of the Meningococcal B vaccine groups for Groups 1 and 2. With a sample size of 60 participants, the probability of observing at least one participant with an adverse event will be more than 90%, if the underlying incident rate is 5%. The analysis for primary endpoints will be descriptive and there has been no formal power calculation to determine the sample size of the trial. The numbers have been therefore chosen based on practical constraints.

Following the updated safety guidance from the JCVI on 8th April 2021 [39], no more participants have been recruited. All the participant aged 6-11 years who randomised to group3 (boosted at 28 days) will be boosted at 112 days. The planned sample size of 75 has been achieved in Groups 1 and 2, and recruitment in Groups 3 and 4 stands at 55 and 56 respectively. As Groups 3 and 4 will both be boosted at D112 post prime, the two groups will be combined for all the safety and immunogenicity analysis. Therefore, the analysis of the younger age cohort will have increased power.

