##### 10.1.2. Immunogenicity

Highly skewed ELISA and neutralising antibody data will be log-transformed prior to analysis. The geometric mean concentration (GMC) and associated 95% confidence interval (CI) will be summarised by computing the anti-log of the mean of the log-transformed data.

The GMCs and CIs at day 28 post prime and boost, and the proportion of participants seroconverting (defined as a greater than a four-fold rise) from day 0 to day 28 post boost will be computed.

Spike-specific T cell responses (ELISPOT) will be presented as means and confidence intervals, or medians and interquartile ranges if non-normally distributed at all post vaccination time points.

Comparisons of continuous immunogenicity data between groups or different time points will be made using a Mann Whitney U test because the low titres below detection threshold are expected, which will cause a non-normal distribution. Comparison of seroconversion rates will be conducted using a Chi-squared test.

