### **10.4. The Level of Statistical Significance**

There will be no statistical significance testing for primary endpoints of safety. For secondary endpoints of immunogenicity, the level of significant will be two-sided 0.05.

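### Between-group titres get a plain Mann-Whitney test although randomisation is stratified by site, and no D112:D28 ratio with a confidence interval is planned (minor, free to improve)

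*Protocol*

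**What the plan says.** On allocation, Protocol Section 7.4.7 says "The randomisation will be stratified by recruitment site and age group" and "A block randomisation with block size of 10 will be applied", in the ratio 4:1:4:1. Section 10.1 gives "60 participants in ChAdOx1 nCoV-19 groups and 15 in each of the Meningococcal B vaccine groups for Groups 1 and 2".

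On analysis, Section 10.1.2 says "Comparisons of continuous immunogenicity data between groups or different time points will be made using a Mann Whitney U test", giving as its reason "because the low titres below detection threshold are expected, which will cause a non-normal distribution". For seroconversion it says "Comparison of seroconversion rates will be conducted using a Chi-squared test". Neither sentence mentions site. The planned summaries are "The GMCs and CIs at day 28 post prime and boost, and the proportion of participants seroconverting", that is, estimates within each group. No ratio or difference between groups with its own interval appears. Section 10.4 adds: "For secondary endpoints of immunogenicity, the level of significant will be two-sided 0.05".

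Section 10.1 also explains that Groups 3 and 4 will both be boosted at D112 and analysed together. Section 10 presents its methods as a summary, with a detailed analysis plan to be signed before any analysis.

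**The concern.** With Groups 3 and 4 merged, Group 1 against Group 2 in 12-17 year olds is the only randomised evidence in this trial on the booster interval. Two features of Section 10.1.2 serve that comparison poorly.

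First, participants are allocated within site in blocks, but the named test pools all sites. Blocking removes chance imbalance between sites, yet the pooled test still treats between-site variation as noise. Its p-value is then somewhat larger than it need be. Age group is constant in this comparison, so site is the only stratification factor at issue.

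Second, a Mann-Whitney test returns a p-value and no effect size. The trial has no formal power calculation, so a p-value alone says little about how far a D112 boost raises titres over a D28 boost. The useful result is a fold-difference with an interval, and none is planned.

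**Working it through.** **The plan's own figure.** The only sample-size figure concerns adverse events: 1 − 0.95^60 = 0.954, which agrees with the stated probability above 90%. No power is stated for immunogenicity, so there is nothing further to reproduce.

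**Inputs from the protocol.**
- 60 ChAdOx1 recipients in each of Groups 1 and 2.
- Four recruitment locations (Section 5).
- A full block of 10 at 4:1:4:1 puts 4 ChAdOx1 recipients in each interval arm, so the arms are nearly balanced within site.
- Adult geometric mean titres (GMTs) 28 days after dose 2 (Table 1b): 22,222.73 (20,360.50 to 24,255.3), N = 443, for intervals under 6 weeks; 63,181.59 (55,180.1 to 72,343.4), N = 154, for intervals over 12 weeks.

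**Inputs assumed.**
- The adult spread applies to adolescents.
- Site explains 0-20% of log-titre variance.
- ChAdOx1 recipients per arm at the four sites are 24, 16, 12 and 8.
- There is no dropout, except where 40 per arm is shown.

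**Spread.** SD(ln) = [ln(upper) − ln(lower)] / (2 × 1.96) × √N.
- Under 6 weeks: 0.1750 / 3.92 × √443 = 0.94.
- Over 12 weeks: 0.2708 / 3.92 × √154 = 0.86.
- Pooled: √[(0.94² + 0.86²) / 2] = 0.90, or 0.39 on the log10 scale.

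**Adult ratio.** 63,181.59 / 22,222.73 = 2.84. The standard error of its log is √(0.94²/443 + 0.86²/154) = 0.082, giving a 95% interval of 2.42 to 3.34.

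**Precision of a D112:D28 ratio.** The 95% interval factor is exp(1.96 × 0.90 × √(2/n)).
- n = 60 per arm: 1.38.
- n = 40 per arm: 1.48.

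Adjusting for site multiplies the exponent by √(1 − R²), where R² is the site share. At R² = 0.05 the factor is 1.37 and at 0.15 it is 1.35. The equivalent sample size is 60 / (1 − R²), or 63 to 71 per arm.

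**Test performance.** 6,000 simulated trials of 60 against 60, normal log titres, site effects drawn at random, two-sided 0.05. Each cell is plain Mann-Whitney / site-stratified van Elteren.

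| Site share | Type I error | Power, ratio 1.5 | Power, ratio 2.84 |
|---|---|---|---|
| 0% | 0.046 / 0.045 | 0.661 / 0.646 | 1.00 / 1.00 |
| 5% | 0.042 / 0.048 | 0.667 / 0.669 | 1.00 / 1.00 |
| 10% | 0.041 / 0.048 | 0.680 / 0.696 | 1.00 / 1.00 |
| 20% | 0.036 / 0.049 | 0.696 / 0.746 | 1.00 / 1.00 |

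Simulation error is about 0.003 for type I error, √(0.05 × 0.95 / 6000), and 0.006 for power, √(0.67 × 0.33 / 6000).

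With only four sites, randomly drawn effects give a realised share that varies from trial to trial. Holding it fixed at 20% makes the plain test more conservative (type I error 0.028) and raises the gain at a ratio of 1.5 to about 7 points. Hence the ranges of 2-3 points at 10% and 5-7 at 20%.

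**The case against.** The strongest reply is that Section 10 is a summary and defers detail to an analysis plan not shown here. Covariate adjustment and the effect measure are often settled there. This has weight, and the plan may already do what is asked. But the protocol does name the test. A plan that follows it literally uses an unstratified rank test, and one that departs from it will disagree with the protocol.

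Several stronger readings are tempting, and the protocol does not support them.

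- *The analysis is biased or invalid because it ignores the stratification.* It is not. Blocking keeps the arms balanced within site, and type I error stays at or below 0.05. The stratification sentence in Section 7.4.7 is itself sound.
- *The plan gives no information on the interval effect.* GMCs with 95% intervals are planned per group, so a reader can form the ratio. What is missing is an interval for that ratio.
- *The reason given for a rank test is wrong.* It is sound for baseline, post-prime and MenB data. The protocol's adult data show neutralising antibody in 32 of 35 after one dose. It fits poorly only for boosted ChAdOx1 recipients, since 35 of 35 adults responded after the booster.
- *The trial's stated aim is to compare the intervals.* The secondary objective is to assess immunogenicity under both schedules. It sets no D28-against-D112 estimand, and Section 10.1.2 does not name the contrast.

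It is also fair to say that the power gain may be nil. If site explains no variance, the stratified test is about 1 point worse.

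**Conclusion.** The point stands as a minor one. The plain Mann-Whitney test is valid but slightly conservative under site-stratified allocation, and the protocol plans no between-group estimate with an interval for its one remaining randomised booster-interval comparison. The missing estimate matters more than the missing stratification.

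For a GMC ratio of 1.5, stratifying changes power by about nil at a 0-5% site share, +2-3 points at 10% and +5-7 at 20%. At 2.84 both tests have power near 1. The added ratio would carry an interval of about ×/÷1.38 with 60 per arm. It would be nearer ×/÷1.48 with 40, should declined boosters (Section 6.3.6) or the seronegative, two-dose analysis set (Section 10.2) cut numbers that far.

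These figures rest on the adult spread in Table 1b and on assumed site sizes and site shares. The direction (conservative, not inflated) held at every non-zero share examined; its size cannot be fixed from the protocol.

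**What to change.** In Section 10.1.2, or in the analysis plan with the protocol wording aligned:

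1. For post-boost comparisons between vaccinated groups, report the D112:D28 GMC ratio with a 95% interval from a linear model of log titre on group with site as a covariate.
2. Make the supporting rank test site-stratified (van Elteren).
3. Keep a rank test where values below detection are expected: baseline, post-prime and MenB comparisons. State how any such value enters the log-titre model.

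The cost is wording only, with no new data or visits. Very small sites may need merging under a rule set before analysis, and precision is marginally lower if site explains no variance.

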#### **6.3.2. Exclusion Criteria**

The participant may not enter the study if any of the following apply:

- Child of an staff member of the Oxford Vaccine Group
- History of laboratory confirmed COVID-19 (A positive result on a validated test for SARS-CoV-2 or seropositivity for SARS-CoV-2 before enrolment)
- Chronic respiratory diseases, including mild asthma (resolved childhood asthma is allowed)
- Prior receipt of MenB vaccine
- Prior receipt of any vaccines (licensed or investigational)  $\leq 30$  days before enrolment
- Planned receipt of any vaccine other than the study intervention within 30 days before and after each study vaccination
- Prior receipt of an investigational or licensed vaccine likely to impact on interpretation of the trial data (e.g. Adenovirus vectored vaccines, any coronavirus vaccines)

- Administration of immunoglobulins and/or any blood products within the three months preceding the planned administration of the vaccine candidate
- Any confirmed or suspected immunosuppressive or immunodeficient state, including HIV infection; asplenia; recurrent severe infections and use of immunosuppressant medication within the past 6 months, except topical steroids or short-term oral steroids (course lasting <14 days)
- Any autoimmune conditions,
- History of allergic disease or reactions likely to be exacerbated by any component of the ChAdOx1 nCoV-19 or MenB vaccines
- Previous diagnosis of Kawasaki disease
- Any history of angioedema
- Any history of anaphylaxis
- Pregnancy, lactation or willingness/intention to become pregnant during the study
- Any history of cancer
- Bleeding disorder (e.g. factor deficiency, coagulopathy or platelet disorder), or prior history of significant bleeding or bruising following IM injections or venepuncture
- Any other serious chronic illness requiring hospital specialist supervision
- Congenital cardiovascular conditions
- Any other significant disease, disorder or finding which may significantly increase the risk to the participant because of participation in the study, affect the ability of the participant to participate in the study or impair interpretation of the study data.

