#### 7.4.2.1. Vaccination - D0

All vaccines will be administered intramuscularly according to specific SOPs. Observations will be taken 60 minutes after vaccination (+/- 30 minutes) and the sterile dressing removed and injection site inspected.

In all groups, participants or their parent/guardian will be given an oral thermometer, tape measure and diary card (paper or electronic), with instructions on use, along with the emergency 24-hour telephone

number on the contact card to contact the on-call study physician if needed. For participants aged under 16, it is expected that parents/guardians will communicate with the trial team by telephone and fill in the diary card. Participants aged 16 and over will be expected to fill in their own diary card and communicate with the study team directly.

Participants or their parent/guardian will be instructed on how to self-assess the severity of these AEs. There will also be space on the diary card to self-document unsolicited AEs, and whether medication was taken to relieve the symptoms. Diary cards will collect information on the timing and severity of the following solicited AEs.

In keeping with PHE guidance on vaccine associated fever during the pandemic [36], participants experiencing fever within the first 48 hours of vaccination, with no other primary symptom of COVID-19 (cough, anosmia, ageusia) will not be required to self-isolate unless there is otherwise clinical suspicion of COVID-19.

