### **8.5. Control Vaccine**

Participants who are allocated to the control groups will receive two injections of MenB vaccine instead of ChAdOx1 nCoV-19.

Participants will be blinded as to which intervention they are receiving. A vaccine accountability log of MenB will be maintained. There will be no additional labelling of these vaccines beyond their licensed packaging.

MenB will be stored in a locked (or access controlled) refrigerator (2°C – 8°C) at the sites, as per SmPC.

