## 8.9. Provision of Treatment for Controls

If any other vaccine shown to be efficacious at preventing COVID-19 disease is licensed for this age group during the course of this study, then participants will not be disadvantaged by their participation in the trial. Unblinding will be offered upon discussion, to facilitate participation in any national immunisation programme that is implemented. All those in the control group will be offered a full course of the IMP (ChAdOx1 nCoV-19) at the end of the study if they are not eligible for a vaccine under national immunisation guidelines, should it be approved for use in the age group. All those in the intervention arms will be offered Bexsero at the end of the study.

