##### 10.1.1. Safety and reactogenicity

All SAEs will be presented for each group using descriptive analyses, including any evidence of disease enhancement, hospital admissions and cases of suspected PIMS-TS.

Counts and percentages of each local and systemic solicited adverse reaction from diary cards, and all unsolicited AEs, and SAEs of special interest will be presented for each group.

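### Sections 7.4.7 and 8.9 give different rules for unblinding a child who could have a national COVID-19 vaccine; separately, second doses given after unblinding are not kept apart from blinded ones in the primary safety counts

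*Protocol*

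**What the plan says.** On unblinding, section 7.4.7 reads "If a participant becomes eligible for routine immunisation then they will need to be unblinded". It sets no condition on the child's wish or arm. Section 8.9 deals with another efficacious vaccine being licensed for the age group during the study, and reads "Unblinding will be offered upon discussion, to facilitate participation in any national immunisation programme that is implemented".

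On what follows, section 7.4.7 says that an unblinded control is advised to have a COVID-19 vaccine under NHS guidelines, and adds "They will also be offered the opportunity to complete their course of MenB vaccination if they have not already received their second dose". For the other arm it says "If participants were in the ChAdOx1 arm, they will be offered the opportunity, in the trial, to complete their course of ChAdOx1 vaccination". All unblinded children may stay for safety and immunogenicity follow-up.

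On the blind and the data, the trial is single-blind. Section 8.5 says "Participants will be blinded as to which intervention they are receiving", and 7.4.7 says that the staff who give the vaccine are not blinded. On the diary, section 7.4.2.1 says "Participants or their parent/guardian will be instructed on how to self-assess the severity of these AEs".

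On the analysis, section 4 defines primary outcomes (a) and (b) as solicited reactions over 7 days after vaccination and (c) as unsolicited events over 28 days. Section 10.1.1 presents "Counts and percentages of each local and systemic solicited adverse reaction from diary cards" for each group, together with all unsolicited events. Section 10.2 puts everyone who had at least one dose into the safety analysis, by vaccine received. Section 10.5 includes all available data.

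**The concern.** There are two separate points.

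First, one section requires what the other only offers. For a child who becomes eligible but would decline the national vaccine, 7.4.7 ends the blind and 8.9 does not. Sites could act differently, and the blind could be lost in children for whom unblinding serves no purpose that 8.9 names.

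Second, the participant's blind is the only one that the protocol states, and the primary outcomes rest largely on that participant's or parent's own report. Most solicited symptoms in Table 4 (pain, fatigue, headache, malaise, nausea) are subjective. A second dose given after unblinding yields an open diary, and no protocol text separates it from a blinded one. There is a related weakness in the control arm. Section 7.4.7 gives no spacing between the advised COVID-19 vaccine and the second MenB dose. If a diary window covered both, reactions to the non-trial vaccine would be counted as control reactions, and ChAdOx1 nCoV-19 would look relatively milder.

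**Working it through.** **The plan's own figure.** Section 10.1 claims more than a 90% probability of seeing at least one participant with an event when n = 60 and the true rate is 5%. 1 − 0.95^60 = 0.954, so the claim reproduces. It is used below only to price the fix.

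**The two unblinding rules side by side.**

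| | Section 7.4.7 | Section 8.9 |
|---|---|---|
| Trigger | Eligibility for routine immunisation | Another efficacious vaccine licensed for the age group |
| Status | Required | Offered after discussion |
| Purpose | Advice that depends on the arm | Access to a national programme |

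Both describe access to vaccination outside the trial. They give different instructions for an eligible child who declines.

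**How open second doses reach the primary counts.**
1. Section 7.4.7 allows the second dose after unblinding. It is expressly in the trial for ChAdOx1; for MenB the setting is not stated.
2. Section 4 attaches outcomes (a) to (c) to vaccination, without limiting them to blinded doses.
3. Section 10.2 includes everyone dosed, and 10.5 includes all available data.
4. Section 10.1.1 reports by group, with no split by blinding status.

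**How many doses could be affected.** The protocol gives no number, but its dates bound it.
- Assume the last first dose was on 8 April 2021, the date of the guidance after which recruitment stopped (sections 5 and 10.1). Tables 5b to 5d set the booster window at days 112 to 140 after V1.
- 8 April + 112 days = 29 July 2021; 8 April + 140 days = 26 August 2021.
- The only dated offer is 13 September 2021, for ages 12-15 (Appendix A, used for its date only). That is 18 days after the last window closes.
- Adolescents finished earlier. All 150 had to be primed and reviewed at day 7 before the younger sentinel group was enrolled (section 5). Section 3.2 links the added safety bloods to day 7 diaries from the 6-11 year olds, and Appendix A dates that change to 25 March 2021. So the last adolescent first dose was by about 25 March − 7 − 7 days = 11 March. The Group 2 window then closes on 29 July (+140), and its 28-day event collection on 26 August (+28).
- Group 1 was due its boost at day 28-42, so by about 22 April.

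On-schedule boosts therefore precede that offer. What remains is boosters given late (section 6.3.3 permits deferral after a positive PCR) and any eligibility that arose earlier. The documents give no eligibility date for ages 16-17 or 6-11. Amendment 9 (28 May 2021) clarifies that ChAdOx1 recipients unblinded because of the national roll-out can have their second dose in the trial, so such doses were foreseen.

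**What one child can do.** The largest change in a control percentage is 1/15 = 6.7 points in Group 1 or Group 2, and 1/21 = 4.8 points among the 21 controls aged 6-11. Each is reached only if that child's yes/no report for a symptom changes; otherwise the change is zero.

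**Illustration.** The documents give neither the share f of open second doses nor the reporting shift s. A group percentage moves by f × s. Assuming f = 10% and s = 5 points, this is 0.5 points; assuming f = 50% and s = 20 points, it is 10 points. The dates make the upper end implausible.

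**The case against.** The strongest defence has four parts.

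- The wording in 7.4.7 may mean only that a child must be unblinded in order to be vaccinated, since the advice there depends on the arm. That reading is possible, but the text does not state it, and 8.9 is phrased differently. The need to reconcile stands.
- The statistical section is a summary and defers to a detailed analysis plan, where a table by blinding status could sit. That is fair, and it is why the conflict between 7.4.7 and 8.9 is the firmer point. Even so, sections 10.1.1, 10.2 and 10.5 as written include open doses without distinction.
- The dates leave few second doses, perhaps none, affected by the September offer. This stands and limits the size.
- The primary analysis is descriptive (sections 10.1 and 10.4), so no error rate or power is at stake. This also stands.

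Three stronger readings are tempting, and the documents support none of them.

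- A reader might take all 150 adolescents as the number affected. The dated offer covers ages 12-15 only, and on-schedule second doses came before it.
- A reader might infer that 7.4.7 breaks the rule on other vaccines in section 6.3.2, "Planned receipt of any vaccine other than the study intervention within 30 days before and after each study vaccination". That is an entry criterion, repeated as such in 8.8, and 7.4.7 does not contradict it.
- A reader might infer that combining open and blinded diaries causes the wider loss of the blind. It does not: the loss comes from the unblinding rule, and the combined counts are a separate consequence of dosing after unblinding.

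**Conclusion.** The point holds in a limited form. Sections 7.4.7 and 8.9 conflict on whether unblinding is required or offered, and they use different triggers. Read literally, 7.4.7 unblinds children who would not take up a national offer. Separately, the safety analysis as written would count second-dose diaries completed after unblinding with blinded ones in primary outcomes (a) to (c).

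The likely effect on the results is small. It is capped at 6.7 or 4.8 points per control child whose report changes, and the number of such children is not given. Calling it small rests on two assumptions: that first doses ended by about 8 April 2021 and that boosters were given within their windows. The direction of any bias from open reporting cannot be told from the documents. For a control diary that overlaps a COVID-19 vaccine, it would favour ChAdOx1. The change is worth making because it is nearly free and protects participant-reported primary outcomes.

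**What to change.** 1. Reconcile sections 7.4.7 and 8.9 into one unblinding rule with one stated trigger. It should say whether unblinding is required or offered, and what happens to an eligible child who declines.
2. State in 7.4.7 whether a MenB second dose after unblinding is given within the trial.
3. Flag each second dose given after unblinding, and each diary that overlaps a non-trial vaccine. In the tables under 10.1.1, show these apart from blinded second doses, for both solicited and unsolicited events.

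The cost is a wording change and a flag in the safety tables, with slightly fewer children in the main second-dose table. No sample size changes. In a ChAdOx1 group of 60, the claim of more than 90% still holds for blinded second doses alone if at least 45 remain: 1 − 0.95^45 = 0.901, against 1 − 0.95^44 = 0.895. Up to 15 of 60 could therefore be shown separately.
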